#### Mortality cohort

Neonatal mortality is ascertained using abstracted, deidentified data from the eCHIS database for clients of CHWs affiliated with study facilities. These participants are not enrolled in the study as human subjects and do not provide consent for study activities.

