## Interventions

### Explanation for the choice of comparators {6b}

Randomization is at the level of the healthcare facility. A cluster-randomized design is used in which entire facilities are randomized because the intervention impacts CHW workflow and therefore affects all households under their care rather than individual clients. The comparison control treatment is the standard of care version of eCHIS which is currently being used by CHWs across Kenya. eCHIS guides CHWs through completing home visits, with a range of workflows including maternal health, child health, nutrition, malaria, and water sanitation and hygiene [46]. This version of eCHIS has no SMS communication between CHWs and clients. In both study arms, antenatal and maternal and child health clinical services continue to be provided through MOH clinics with minimal interactions with study personnel.

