#### Quantitative questionnaires

Quantitative questionnaires are administered electronically to women, CHWs, and supervisors by study staff using the REDCap platform. Women complete questionnaires during study visits at the facility at enrollment in pregnancy and at 6 weeks postpartum (Table 2). At each visit, a standardized questionnaire is administered to record self-reported outcomes and sociodemographic and clinical characteristics that may be associated with them. Outcomes include timing of breastfeeding initiation, introduction of complementary foods, application of substances to the umbilical cord, knowledge of eight danger signs (not feeding, high temperature, low temperature, fast breathing, difficulty breathing, not moving, convulsions, and jaundice) [53], timing of first bath, attending facility-based care during illness episodes, and acceptability of CHV-NEO, using the AIM [48]. Associated demographic and clinical factors include maternal education, income, employment, parity, distance from home to clinic, intimate partner violence, depression symptoms, past healthcare experience, parental self-efficacy, and infant sex.

CHWs and supervisors complete questionnaires annually: at study launch, 1 year, and study close (Table 2). Questionnaires include outcomes as well as demographic and professional characteristics that may be associated with outcomes. Outcomes include acceptability of CHV-NEO, assessed using the AIM measure [48], and time spent on work duties in the prior 2 weeks. Characteristics that may be associated with outcomes include professional background, training, and experience and comfort with the eCHIS platform.

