#### Methods in the analysis to handle protocol non-adherence and any statistical methods to handle missing data {20c}

Based on the Mobile WACh NEO RCT [41], we expect a 10% loss to follow-up between enrollment and the 6-week study visit. We anticipate that women who are lost to follow-up are more likely to be disengaged from care and have experienced adverse outcomes. We also anticipate missingness may differ by arm, with the intervention arm having higher retention. A secondary analysis of mortality will be performed in which missing mortality at 28 days will be imputed using multiple imputations by chained equations (MICE).

To explore any dose–response effects associated with variation in the fidelity of intervention delivery, we will conduct an exploratory analysis comparing primary and secondary outcomes between participants who received low vs. high fidelity of the intervention, defined based on the number of automated and CHW messages received. Propensity score matching will be used to control for confounding by participant or CHW characteristics.

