#### Adverse event reporting and harms {22}

Adverse events among perinatal women, CHWs, or supervisor participants are elicited at all study visits and may also be reported spontaneously if a participant contacts the team. All adverse events are recorded by study staff using an electronic REDCap questionnaire based on a phone conversation with the participant. Events to be monitored include maternal and infant death, maternal and infant hospitalization, pregnancy loss, experience of violence, losing housing, breach of confidentiality, and suicidal behavior. Adverse event monitoring in the mortality cohort is more limited because the study will not have direct contact with these individuals. Events monitored in this cohort include maternal and infant death, pregnancy loss, and report of maternal postpartum danger signs at home visits, abstracted from eCHIS. Adverse and severe adverse events will be monitored by the study team, reported to ethical review boards as needed, and unblinded results will be reviewed by the DSMB. The DSMB will make recommendations regarding any imbalances in safety outcomes.

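### The exploratory fidelity analysis of neonatal mortality uses a raw message count, which gestation at birth and the infant's death themselves determine

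*Protocol article*

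**What the plan says.** Under Methods in the analysis to handle protocol non-adherence {20c}, the article states: "we will conduct an exploratory analysis comparing primary and secondary outcomes between participants who received low vs. high fidelity of the intervention". Fidelity is "defined based on the number of automated and CHW messages received", with no time window given. The one stated safeguard is "Propensity score matching will be used to control for confounding by participant or CHW characteristics".

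Three other places bear on this:

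- **Message schedule** (Intervention description {11a}, SMS curriculum). Messages start at 28 weeks and are weekly to 38 weeks, then daily to delivery. After delivery there are two a day for two weeks, then one every other day to six weeks. After a neonatal death the infant messages end and four weekly bereavement messages follow.
- **Source of the primary outcome** (Mortality cohort, under {26a}): "Neonatal mortality is ascertained using abstracted, deidentified data from the eCHIS database for clients of CHWs affiliated with study facilities". Adverse event reporting and harms {22} adds that "the study will not have direct contact with these individuals".
- **Source of maternal covariates** (Quantitative questionnaires, under {18a}): "Associated demographic and clinical factors include maternal education, income, employment, parity, distance from home to clinic", among others. These are recorded at study visits, which only the in-depth cohort attends.

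The section on statistical methods {20a} keeps intention-to-treat for the primary and secondary outcomes.

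**The concern.** A dose-response analysis is informative only if the dose is not itself a product of prognosis or of the outcome. Here it is both. A woman who delivers early has fewer weeks in which to receive messages, and her baby is at higher risk; the Background section itself names complications of preterm delivery as a cause of these deaths. A woman whose baby dies on day 3 receives no further infant messages, so the death lowers her count. Both mechanisms push deaths into the low-fidelity group. The comparison would then favour high fidelity even if the messages did nothing, and on the trial's primary outcome.

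Matching is meant to deal with confounding, but the maternal covariates the article lists belong to a different dataset from the one that holds the mortality outcome.

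**Working it through.** The plan states no figure for this analysis, so there is none to reproduce. The power statement in Sample size {14} concerns the randomised comparison and plays no part here.

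**1. Scheduled antenatal messages, for a woman enrolled by 28 weeks**

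- Birth at 34 weeks: 34 − 28 = 6.
- Birth at 38 weeks: 38 − 28 = 10.
- Birth at 40 weeks: 10 + 14 daily = 24.

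**2. Scheduled postnatal messages**

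- Infant surviving to six weeks: 2 × 14 + 28/2 = 28 + 14 = 42.
- Infant dying on day 3: 2 × 3 = 6, plus 4 bereavement messages = 10.

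The gap of 32 exceeds the whole antenatal allowance of a 40-week pregnancy. (Assumption: the modified preterm and low-birthweight track keeps the same frequency; the article does not say.)

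**3. Antenatal count, no SMS effect.** Assumptions not in the documents: gestation Normal(39.2, 1.9) truncated at 28.1 to 42.5 weeks, which gives about 12 to 13% preterm; every scheduled message received; split at the median. Overall mortality is set at the article's 10.3 per 1000. Ratios over repeated runs:

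| Assumed preterm/term risk ratio | Low/high mortality ratio |
|---|---|
| 5 | 1.9 to 2.1 |
| 8 | 2.6 to 2.8 |
| 12 | 3.7 to 3.9 |

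Staggering registration between 12 and 36 weeks leaves these almost unchanged (2.0, 2.7, 3.7). With no preterm excess the ratio is about 1 (0.98 to 1.02), so this part rests wholly on the preterm assumption. These are unmatched ratios.

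**4. Total count to six weeks, no SMS effect and no preterm excess.** Assumptions: delivery Normal(39, 1.5) weeks, registration uniform over 20 to 36 weeks, mean of 3 CHW messages, median split. Rates are per 1000, with overall mortality 10.3 per 1000:

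| Assumed timing of deaths | Low | High | Ratio |
|---|---|---|---|
| Uniform over 28 days | 17.9 | 3.31 | 5.4 |
| 75% in week 1 | 20.5 | 1.15 | about 18 |

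At 21.0 per 1000 the ratios are 5.5 and 17.2. In a further run that also allowed a preterm excess, the ratio for total counts stayed at about 18 to 21 within term births alone. Handling gestation therefore does not remove this part.

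**5. Covariates.** Mortality comes from de-identified eCHIS records on women the study does not contact. Education, income, parity and distance come from in-depth questionnaires. No link is described. CHW characteristics are collected from CHWs, and gestational age, delivery date and delivery outcome are in eCHIS, so the propensity model for mortality is limited but not empty.

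The documents do not allow the residual confounding to be computed. For illustration, take an unmeasured factor with mortality ratio R and prevalence p₁ in low-message and p₀ in high-message women. The bias factor is [1 + p₁(R − 1)]/[1 + p₀(R − 1)]. With R = 2, p₁ = 0.4, p₀ = 0.2 it is 1.4/1.2 = 1.17. With R = 3, p₁ = 0.5, p₀ = 0.2 it is 2.0/1.4 = 1.43.

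Restricting the mortality analysis to in-depth women would not help. About 1000 in the intervention arm yield 1000 × 0.0103 = 10 to 1000 × 0.021 = 21 deaths, against 37 to 76 among about 3600 in the full arm.

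**6. Repaired exposure.** With messages received out of messages scheduled up to delivery, a no-effect simulation gave ratios of about 0.93 to 0.97. That is close to 1. The proportion is coarse when few messages are scheduled, which is a reason to match on gestational age as well.

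**The case against.** The other side has real points.

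- **The analysis is exploratory.** This stands. A reader might infer that the randomisation is discarded. It is not: intention-to-treat remains the analysis of the primary and secondary outcomes. Nor does the article say this comparison would be used to explain a null result.
- **Gestation is in eCHIS.** This stands. The article speaks of participant characteristics, not baseline ones, so gestational age at birth could enter the match. In the simulation of step 3 that would remove the whole distortion. It does nothing for the dependence on death in step 4.
- **Covariates and time window may be detailed elsewhere.** This stands in part. A condensed article need not list the propensity model, nor does it list every eCHIS field. A reader might infer that women certainly stay confounded by wealth, literacy or phone access. That is plausible, but its size cannot be computed. If a fuller document limits the count to the antenatal period, the death problem disappears and the gestation problem remains unless matched. As published, the exposure is simply the number received.
- **Replacing the analysis with a complier-average effect.** A reader might want this, since control "This version of eCHIS has no SMS communication between CHWs and clients" makes cluster assignment a natural instrument. It answers a different question, however: the effect of enrolment, not whether outcomes vary with fidelity among recipients. Its exclusion restriction is also doubtful, because intervention CHWs receive an extra training day, SMS supervision prompts and performance feedback that could reach women who never enrol.

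**Conclusion.** The concern holds for the mortality part of the exploratory fidelity analysis. As published, the exposure is partly a consequence of the outcome and of a strong risk factor for it, and the bias runs towards a benefit of high fidelity.

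Under no true effect the spurious low-to-high ratio is about 2 to 4 for an antenatal count, given an assumed preterm risk 5 to 12 times term. It is about 5 to 18 for a total count, given the assumed timing of deaths. Both simulations let every scheduled automated message arrive. Wide real variation in receipt would dilute the ratios but not reverse their direction. The dependence on death follows from the article's schedule alone and needs no assumption about preterm risk.

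The covariate gap is secondary. It limits what matching can achieve for mortality, by an amount the documents do not fix. It does not affect the secondary outcomes, whose covariates come from the same in-depth questionnaires. The main intention-to-treat analysis is untouched. The wording should be changed, but the trial's primary conclusion does not depend on it.

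**What to change.** Amend {20c} as follows.

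1. **Mortality.** Define exposure as SMS enrolment before birth, or as messages received divided by messages scheduled up to delivery. Exclude all postnatal messages. Match on the eCHIS and CHW characteristics that exist for this cohort, name them, and include gestational age at birth. Enrolment before birth also needs this match, since a shorter pregnancy leaves less time to enrol.
2. **Secondary outcomes.** Keep propensity matching in the in-depth cohort, where the questionnaire covariates are available, with exposure expressed as messages received out of messages scheduled.
3. **Optional.** Add, without substituting it for the above, a complier-average effect with cluster assignment as instrument. State that the extra training and supervision may breach its exclusion restriction.

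Cost: revised analysis wording and slightly more analysis work, using message and delivery data already held in eCHIS. The exposure contrast will be smaller than with raw counts, and any complier estimate will have a wider interval than intention-to-treat, which stays the main analysis.

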#### Plans to give access to the full protocol, participant-level data, and statistical code {31c}

De-identified data, statistical code, and the study protocol will be made available to the public upon publication of the results.

### Oversight and monitoring

#### Composition of the coordinating center and trial steering committee {5d}

The University of Washington, Kenyatta National Hospital, and Medic teams all contribute to trial organization and daily support. Day-to-day trial operations are undertaken by data collectors, a data manager, and a research coordinator based in Kisumu County. This team meets with the rest of the team (research coordinator, research scientists, design specialists, co-investigators, and principal investigators) weekly to report on progress and review data.

#### Composition of the data monitoring committee, its role, and reporting structure {21a}

The CHV-NEO study has engaged an independent Data Safety Monitoring Board (DSMB) to act in an advisory capacity to monitor patient safety and evaluate the efficacy of the intervention. The responsibility of the DSMB is to review interim safety and efficacy at periodic intervals (6-monthly intervals after initiation of the trial). The Data Safety Monitoring Board consists of physicians, statisticians, neonatologists, and digital health specialists selected by the study team. Membership consists of persons completely independent of the investigators who have no financial, scientific, or other conflict of interest with the trial. Members are not current or past collaborators or associates of the University of Washington or Kenyatta National Hospital principal investigators.

#### Adverse event reporting and harms {22}

Adverse events among perinatal women, CHWs, or supervisor participants are elicited at all study visits and may also be reported spontaneously if a participant contacts the team. All adverse events are recorded by study staff using an electronic REDCap questionnaire based on a phone conversation with the participant. Events to be monitored include maternal and infant death, maternal and infant hospitalization, pregnancy loss, experience of violence, losing housing, breach of confidentiality, and suicidal behavior. Adverse event monitoring in the mortality cohort is more limited because the study will not have direct contact with these individuals. Events monitored in this cohort include maternal and infant death, pregnancy loss, and report of maternal postpartum danger signs at home visits, abstracted from eCHIS. Adverse and severe adverse events will be monitored by the study team, reported to ethical review boards as needed, and unblinded results will be reviewed by the DSMB. The DSMB will make recommendations regarding any imbalances in safety outcomes.

#### Frequency and plans for auditing trial conduct {23}

No audits are planned.

#### Plans for communicating important protocol amendments to relevant parties (e.g., trial participants, ethical committees) {25}

Modifications and amendments to study protocols are submitted to the University of Washington Institutional Review Board and Kenyatta National Hospital Ethics Review Committee before implementation. Once approved, participants are informed and re-consented at scheduled study visits, as needed, to align with updated protocols. Changes are communicated to the DSMB at regularly scheduled meetings. Trial registries are reviewed and updated by the study team yearly during the study period.

#### Dissemination plans {31a}

We will disseminate results to a community advisory board, made up of medical providers and community members living in the study area, twice a year. Study findings will be shared with the participating facilities, Kisumu County leadership, and Kenyan Ministry of Health at the study conclusion as a presentation or written report. Findings will be disseminated to the research community in the form of conference presentations and journal articles.

## Discussion

This trial will be the first to evaluate the effect of a text messaging intervention provided by CHWs on neonatal health. Integration of our intervention into the Ministry of Health’s eCHIS, provision of the intervention by County CHWs as part of their routine services, and evaluation of implementation outcomes will ensure that findings from this trial are relevant to routine care provision and readily translated to policy decisions. Findings from this trial have the potential to inform the design and implementation of future text messaging programs with CHWs in LMICs.

## Trial status

We began recruitment on December 11, 2023, and anticipate the completion of data collection in December 2025. The current protocol is version 5, dated 28 November 2023.

## Data Availability

Deidentified data will be made available upon publication of trial findings, in compliance with a data sharing agreement between Kisumu County and the University of Washington.

## Abbreviations

ANC: Antenatal care
eCHIS: Electronic Community Health Information System
ERC: Ethics Review Committee
CHW: Community health worker
IDI: In-depth interview
IRB: Institutional Review Board
LMIC: Low- and middle-income country
MCH: Maternal and child health
MOH: Ministry of Health
RCT: Randomized controlled trial
SMS: Short message service
SOP: Standard operating procedure
WHO: World Health Organization
DSMB: Data Safety Monitoring Board
